**E. Description of Research Protocol**

Overview: This study aims to test whether non-deceptive administration of placebo in patients with allergic rhinitis will be superior to a control group, and if this effect is independent of detailed information on positive effects of placebos.

Design: 60 patients with allergic rhinitis will be randomized to a two-week course of either non-deceptive placebo pill with detailed information on positive effects of placebos, of non-deceptive placebo pill without detailed information on positive effects of placebos, of no treatment plus usual care with detailed information on positive effects of placebos, and of no treatment plus usual care without detailed information on positive effects of placebos. All groups will receive the same amount of time with the practioner. Participants will be assessed at baseline and at the end of the two weeks.

Design and intervention:

Description of the open-label placebo treatment arms:

After signing the informed consent the patients will be assessed with respect to their allergic symptoms and quality of life. They will be told to note their allergic complaints at the end of each day in an allergic diary. Then they will receive 28 placebos in a white box, labeled with the logo of the university and the following information “Placebo pills (28), take one in the morning and one before night, for 14 days”

Description of the no treatment usual care control arms:

This control group will be treated as the open-placebo group, but do not receive any placebos. The purpose of this control group is to match for time with practioner and to assess general improvements of allergic symptoms due to changes in weather (pollen) conditions.

Description of the detailed information on placebo arms:

After signing the informed consent, patients will be informed about the power of placebos. They will be told that placebos are inactive substances and that they contain no medications. Although placebos contain no medication, placebo effects may still be powerful. The effect will be explained to them by pointing out that the body may automatically respond to taking placebo pills, like Pavlov’s dogs that salivated when they heard the bell. In addition, they will be told that a positive attitude may be helpful for the placebo effect, but is not necessary. Last, they will be instructed that those participants who will be in the placebo group need to take the placebos faithfully. These four statements are identical to the instruction used in previous studies on open-placebos. The further treatment is outlined above.

Description of the detailed information on placebo arms:

Same as before, but here the description of the power of placebos (as outlined above) will be omitted.

Randomization: Will be done by using sealed envelopes indicating the group assignment.

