**B. Background for the Study**

Recent research has demonstrated that placebo treatment can have significant impacts for a wide variety of symptoms (Finiss et al., 2010). Unfortunately, in the traditional understanding response to placebos requires deception. This may cause problems with respect to patient-healthcare provider relationship and ethical difficulties. In contrast to this classic view recent research has demonstrated that placebos may work even without concealment. For example, Kaptchuk et al. (2010) conducted a randomized controlled trail including patients with irritable bowel syndrome. Half of the patiens received placebos without deception, the other half served as a control group. The authors found significantly higher mean global improvement scores, reduced symptom severity, and better quality of life scores for the open-placebo group. Similar results have been reported, for example, for patients with major depression (Kelley et al., 2012) and ADHD (Sandler et al., 2008).

Our previous study has demonstrated that open-label placebos also improve

symptoms in patients with allergic rhinitis (Schaefer et al., 2016). However, this pilot study was based on only few patients. Thus, we here want to replicate the results in a larger sample.

Furthermore, the mechanism of open-label placebo effects remains unclear. Are open-label placebo effects based on bottom-up mechanisms, such as classical conditioning? Or are they linked to raised expectancies about the positive effects of placebos in general, hence representing top-down effects? The latter may be related to the detailed information on the power of placebo effects. This information is included in nearly all open-label placebo studies. In order to disentangle top-down and bottom-up effects, we aim to manipulate this information: Half of the participants will be informed about the power of placebos, the other half not.

We expect to replicate the previous findings that open-label placebos improve allergic symptoms more than in a control group with comparable patient-healthcare provider relationships. Furthermore, we assume that the open-label placebo effect is independent of the information how powerful placebos are, thereby suggesting a bottom-up effect.

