**D. Hypothesis**

In allergic rhinitis patients, a two weeks course of open-label non-deceptive placebo treatment will be superior to no treatment plus usual care control. In addition, information on the positive effects of placebos will not interact with this open-label placebo effect.

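### The information factor is set once at the first visit, and the visible protocol neither limits nor records what uninformed pill patients learn about placebo effects before the two-week outcome

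*Protocol*

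**What the plan says.** Section E of the Protocol randomises 60 patients to four arms: pill or no pill, with or without the talk on placebo effects. The uninformed arms are defined only by what is left out at the first visit: "Same as before, but here the description of the power of placebos (as outlined above) will be omitted". Both pill arms then take home a box that reads "Placebo pills (28), take one in the morning and one before night, for 14 days".

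Between visits the only record is a symptom diary: "They will be told to note their allergic complaints at the end of each day in an allergic diary". Section F lists two outcome measures, the symptom questionnaire (primary) and the SF-36, each taken at baseline and endpoint. Neither asks what patients know, have heard or expect. The analysis is a three-factor ANOVA (time, placebos, information), two-sided at .05.

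Section D predicts a null for the information factor: "information on the positive effects of placebos will not interact with this open-label placebo effect". Section B says what that null would mean: "we assume that the open-label placebo effect is independent of the information how powerful placebos are, thereby suggesting a bottom-up effect".

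**The concern.** The factor is fixed on day 0 and its consequence is measured on day 14. Only the uninformed pill arm combines two weeks of handling a box marked as placebo with having been told nothing about placebo effects. A patient in that arm may look the subject up or ask someone, and from then on is partly informed.

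Contamination usually works against a trial's hypothesis and is conservative. Here it works for the hypothesis. If the effect does depend on information, learning in the uninformed pill arm has two results: it shrinks the interaction, and it creates a pill effect among patients counted as uninformed. Together these look like the predicted finding, an effect independent of information. Nothing collected would separate that from true independence. Because the exposure arises after randomisation, screening for prior knowledge at entry would not catch it.

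**Working it through.** **The plan's own figure.** Section F gives 104 as the required total, without effect size, SD, power or test, so it cannot be reproduced. Read as two groups of 52, two-sided .05, at an assumed 80% power, it implies a standardised effect of (1.960 + 0.842) x sqrt(2/52) = 0.55 SD. That serves below as one plausible size.

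**Inputs**
- 60 patients (Sections E and F), half of them informed (Section B). Equal cells of 15 are assumed; the Protocol does not state them.
- Two time points, so the three-way term equals the placebo x information interaction on change scores, here in SD units of change.
- Two-sided .05; error df = 60 - 4 = 56.
- True interaction E: 1.0 SD (assumed) and 0.55 SD (the whole pill effect implied above).
- Exposed share c of the uninformed pill cell: assumed, since the Protocol gives no rate.

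**Model.** Information acts only through the pill, and what an exposed patient learns acts like the script. The informed pill effect is then E. The uninformed pill effect is 0 without exposure and cE with it. The expected interaction is E - cE = E(1 - c).

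**Precision.** The interaction is a difference of differences over four cells, so SE = sqrt(4/15) = 0.516 SD. The 95% half-width is 2.003 x 0.516 = 1.03 SD.

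**Power** (noncentral t, 56 df, noncentrality E(1 - c)/0.516):

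| c | Interaction, E = 1.0 | Power | Interaction, E = 0.55 | Power |
|---|---|---|---|---|
| 0 | 1.00 | 48% | 0.55 | 18% |
| 0.2 | 0.80 | 33% | 0.44 | 13% |
| 0.3 | 0.70 | 27% | 0.385 | 11% |
| 0.5 | 0.50 | 16% | 0.275 | 8% |

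With E = 1.0, the uninformed pill cell also shows a pill effect of 0.2, 0.3 or 0.5 SD that comes entirely from information.

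**Two separate effects.** The first row is the sample-size problem: even with no exposure, a true 1 SD interaction is missed slightly more often than not. The rows below add a bias. More patients would narrow the interval but would leave the expected value at E(1 - c).

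**The case against.** - **The label is not an error.** The treatment is open-label and both pill arms receive the same box. This stands. The gap is the missing instruction and record, not the wording on the box.
- **An instruction may exist elsewhere.** Consent pages were removed before review and could ask patients not to discuss the study or look things up. A reader might infer that nothing discourages learning; the visible text cannot prove that. Such a request would still not supply an endpoint record, and Section F lists only two outcome measures.
- **Patients need not know each other.** Section G mentions fliers at the local university and social media. A reader might infer one close community; the text does not say that the social media is the university's, and it gives no evidence of contact.
- **One cell does not decide the contrast.** All four cells enter with equal weight. The focus on the uninformed pill cell rests on the assumption that information acts through the pill.
- **The size is assumed.** Casual or sceptical reading may do less than a talk from the practitioner, so E(1 - c) may overstate the dilution. This stands.
- **Low power dominates.** At 0.55 SD, 20% exposure moves power from 18% to 13%. Removing all exposure would not make a non-significant result interpretable as independence. This also stands, and it limits the weight of the point.
- **Randomisation still gives a valid estimate** of the effect of giving or omitting the script. That is correct, but Section B draws a conclusion about mechanism, which goes further.

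**Conclusion.** The point holds as a cheap improvement, not as a fatal flaw. The Protocol sets the information factor once, reads the outcome two weeks later, and shows no safeguard against, or record of, learning in between. If the effect depends on information, learning in the uninformed pill cell biases the interaction towards the result that the Protocol predicts and interprets, and the planned data could not reveal it.

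The direction assumes that information acts through the pill and that what patients learn resembles the script. The size is unknown: the figures above rest on assumed exposure shares, assumed effects and 15 per cell.

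A reader might go further and infer that exposure will occur to a damaging degree, or that it would be the main cause of a null. The Protocol supports neither: it gives no exposure rate, and low power alone already makes a null likely. An analysis plan, which was not available here, could qualify the interpretation but could not recover answers that were never collected.

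**What to change.** 1. At the two-week visit, after the symptom questionnaire and SF-36 so that the outcomes are not affected, ask all four arms whether they read, heard or talked about placebo effects since the first visit, and whether they expected their assigned condition to help. Report the answers by cell beside the interaction estimate and its confidence interval.
2. In all arms, ask participants not to discuss the study with other participants, or seek information about it, until the final visit. Word this without pointing to placebo effects. It should cover looking things up as well as talking, since the label is more likely to prompt the former.
3. State in Sections B and F that the interaction estimates the effect of giving versus omitting the script, and that a non-significant interaction alone does not establish a bottom-up mechanism.

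Keep patients in their randomised groups and set no exposure cut-off. With about 15 patients in the cell, an observed 3/15 (20%) has an exact 95% interval of about 4% to 48%, too wide to separate tolerable from serious exposure.

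The cost is one instruction, one or two questions and a more qualified conclusion about mechanism. No extra visits or patients are needed.

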**F. Data Analysis**

Outcome Measures: Two outcome measures will be used at baseline and endpoint of this study:

Allergic symptoms questionnaire:

Participants will be asked to assess their allergic symptoms by using a questionnaire describing different symptoms (itching, prickling, or burning feelings in the nose; constipated or running nose; impaired sense of smell or taste; sneezing fits; feeling like having a cold; itching or irritated skin; eczema on the skin; itching, burning or red eyes; billowed eyelids; itching, prickling or scratching feelings in the throat; sore throat; burning feeling or mucus in the mouth or throat; billowed mucosa; breathlessness; cough; headaches; feelings of exhaustion; lack of concentration; tiredness; disorders of the gastrointestinal tract). The patients will indicate their response on a seven-point scale ranging from ‘never’ (1) to ‘always’ (7). For further analysis we will calculate a composite score including all symptoms (see Schaefer et al., 2016). This is the primary outcome parameter.

Quality of Life (SF36): The SF-36 is a German version of the health survey developed by Ware and Sherbourne (1992) in order to examine subjective well-being and quality of life. This instrument assesses the quality of life with respect to the perception of the health both for patients and healthy people. It includes one multi-item scale that assesses different health concepts such as limitations in physical activities because of health problems, limitations in social activities because of physical or emotional problems, limitations in usual role activities because of physical health problems, bodily pain, general mental health (psychological distress and well-being), limitations in usual role activities because of emotional problems, vitality (energy and fatigue), and general health perceptions.

Planned Statistical Analyses

We will conduct analyses of variance (ANOVA) with three factors (time, placebos, information on the power of placebos) for allergic symptoms as well as for quality of life scores. In addition, we will test if baseline scores are different. All tests will be two-tailed with alpha set at .05.

Statistical Power

Based on effect sizes of our previous study (Schaefer et al., 2016), we will need 104 participants for an alpha set at .05. However, given that this is a pilot study and data collection is limited due to weather (pollen) conditions, we aim to include 60 patients in this study.

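### The order of information script, baseline questionnaires and envelope opening is not fixed, and the natural reading lets one randomised factor act before the self-rated baseline

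*Protocol*

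**What the plan says.** Protocol section E describes the four arms as combinations of two factors, pills and information.

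- **Pill arms:** "After signing the informed consent the patients will be assessed with respect to their allergic symptoms and quality of life". Diary instructions follow, and after those "Then they will receive 28 placebos in a white box". The no-pill arms follow the same procedure without the box.
- **Information arms:** "After signing the informed consent, patients will be informed about the power of placebos". The script includes the statement that "those participants who will be in the placebo group need to take the placebos faithfully". The paragraph closes with "The further treatment is outlined above".
- **No-information arms** (the heading repeats that of the information arms): "Same as before, but here the description of the power of placebos (as outlined above) will be omitted".
- **Randomisation:** "Will be done by using sealed envelopes indicating the group assignment". When the envelope is opened, relative to the questionnaires or the script, is not stated.

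Section F makes a self-rated composite symptom score the primary outcome and plans "analyses of variance (ANOVA) with three factors (time, placebos, information on the power of placebos", so baseline is one of the two levels of time. It also plans a test of whether baseline scores differ. Section D states two hypotheses: pills are superior to control, and information does not interact with the pill effect.

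**The concern.** The script is one of the two randomised manipulations, and it is meant to alter what patients expect. The outcomes are self-ratings. If informed patients hear the script before the first questionnaire and uninformed patients hear nothing, the baseline is no longer a pre-treatment measurement for the information factor. Whatever the script does to ratings at once is then subtracted from the change over two weeks.

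The order also bears on allocation. Someone must know whether a patient is to be informed before giving or omitting the script. If the script comes before the questionnaires, at least that part of the allocation is known to staff before baseline is collected.

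At stake is the interpretation of the time x information term. Separating the contribution of the information is a stated aim in sections B and C.

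**Working it through.** **Order of events.** The baseline assessment and the script share one anchor, the signing of consent. The information paragraph gives the script first and then points back to the procedure above it, which begins with the baseline assessment and continues with diary and pills. Read in sequence this gives consent, script, baseline, diary, box. Consent, baseline, script, box also fits the wording, because no sentence places the script before or after the questionnaires. The future tense in the script puts it ahead of entry to the pill or no-pill condition, but says nothing about the questionnaires.

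**What a shifted baseline does.** Let the script shift ratings by *b* at baseline and by *e* at two weeks. The intended information effect is *e*. The time x information contrast estimates *e* − *b*.

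- Transient shift (*e* = 0): the contrast is −*b*, a spurious effect.
- Lasting effect fully present at baseline (*e* = *b*): the contrast is 0, and the effect is masked.

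**Inputs.** The protocol gives 60 patients, half of them informed (sections B and E), and two-sided alpha 0.05 (section F). Assumed here: SD of change 1, equal cells of 15, and the sizes of *b* and *e*. The protocol gives no source for any shift, and it contains no figure on this point to reproduce.

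**Transient shift.** With 30 against 30, SE = √(1/30 + 1/30) = 2/√60 = 0.258. The rejection probability is P(|Z| > 1.96) with Z centred at *b*/0.258.

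| Assumed *b* (SD) | *b*/SE | False-positive rate |
|---|---|---|
| 0 | 0 | 5% |
| 0.1 | 0.39 | 6.7% |
| 0.2 | 0.77 | 12.1% |
| 0.3 | 1.16 | 21.3% |

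**Lasting effect.** Take *e* = 0.5 SD, with a share *c* already present at baseline, so the contrast is 0.5 × (1 − *c*).

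| *c* | Contrast (SD) | Power |
|---|---|---|
| 0 | 0.50 | 49% |
| 0.25 | 0.375 | 31% |
| 0.5 | 0.25 | 16% |
| 1 | 0 | none beyond alpha |

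**The hypothesis terms.** Suppose *b* is the same in informed pill and informed no-pill patients.

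- Time x placebo: the shift enters both sides as *b*/2 and cancels.
- Time x placebo x information: it enters as *b* − *b* = 0.

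If the shift arises in only one informed cell of 15, neither cancels. For 0.3 SD in one cell:

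- Three-way contrast: bias 0.3, SE = √(4/15) = 0.516.
- Time x placebo: bias 0.15, SE 0.258.

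Both ratios are 0.58, which gives about 9% false positives for each term.

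**The planned baseline test.** With 30 against 30 and a baseline SD of 1, it would flag a shift of 0.25 SD about 16% of the time and one of 0.5 SD about 49% of the time. It also could not tell a shift caused by the script from chance imbalance.

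**The case against.** The strongest reply is that the protocol never says the script precedes the questionnaires. The sentence that points back speaks of treatment, which could mean pills or no pills and not the assessment. This stands: a reader might infer that the protocol prescribes a manipulation before baseline, but it only leaves that order open and favours it in sequence.

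Second, the false-positive figures concern a term that tests neither hypothesis in section D. This also stands. A reader might go further and infer that the pill effect or the interaction is biased because patients already know their allocation when they rate baseline. The documents do not support that. The box comes after the assessment, the script refers generically to those who will be in the placebo group, and the time of envelope opening is simply absent. Even known allocation would only permit unequal shifts between pill and no-pill arms, not guarantee them.

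Third, the script is mostly about responses to pills not yet taken, so an immediate change in ratings of symptom frequency is possible but not shown. That is fair, and it is why the shift sizes are assumptions.

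The reply does not remove the defect. On either reading, the order of baseline, allocation and one randomised manipulation is unfixed, and nothing protects the baseline from the information factor.

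**Conclusion.** The point holds as an unfixed sequence whose natural reading is harmful, not as a documented error of order. If the script comes first, the time x information term is distorted in a direction that depends on how long the shift lasts. A transient shift of 0.1 to 0.3 SD raises the false-positive rate to about 7 to 21%. If half of a lasting 0.5 SD effect is already present at baseline, power falls from 49% to 16%. These figures rest on the assumed shifts, a change SD of 1 and 30 against 30.

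The tests of the two stated hypotheses are unaffected if the shift is equal in pill and no-pill arms, and the protocol gives no direct evidence that it would differ. No figure in the protocol is wrong because of this point. It is still more than a missing detail, since the order of procedures decides whether the baseline is a true baseline, and the planned baseline test would often miss the problem.

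**What to change.** Rewrite the arm descriptions in section E as one visit sequence that applies to all four arms:

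1. Informed consent.
2. Baseline symptom questionnaire and SF-36.
3. Opening of the envelope.
4. The information script, or its omission.
5. The box of pills, or no box.

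This keeps both randomised factors, and staff knowledge of the allocation, away from the baseline ratings. A second set of envelopes is not needed for this purpose. The heading of the no-information arms should be corrected at the same time. The cost is a short rewrite and, at most, a reordering of one visit. It adds no visit time and changes no study treatment.

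### As written, the envelope procedure lets the practitioner know the pill arm while giving the information script and the matched contact, before that knowledge is needed; disclosing the two factors in two stages would prevent this at little cost

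*Protocol*

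**What the plan says.** Section E of the protocol (Description of Research Protocol) makes the four combined groups the unit of allocation: "60 patients with allergic rhinitis will be randomized to a two-week course of either non-deceptive placebo pill with detailed information on positive effects of placebos", followed by the other three combinations. The Randomization line in the same section reads in full: "Will be done by using sealed envelopes indicating the group assignment".

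The order of the visit comes from the arm descriptions in section E. For the informed arms, "After signing the informed consent, patients will be informed about the power of placebos", and the rest of the visit follows. The script closes with a conditional statement: "Last, they will be instructed that those participants who will be in the placebo group need to take the placebos faithfully". The pill box is handed over after the symptom and quality-of-life assessment and the diary instruction.

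On comparability, section E says of the controls: "This control group will be treated as the open-placebo group, but do not receive any placebos". It adds that "All groups will receive the same amount of time with the practioner" and that "The purpose of this control group is to match for time with practioner" (together with capturing changes due to pollen conditions). Section B (Background for the Study) expects open-label placebos to "improve allergic symptoms more than in a control group with comparable patient-healthcare provider relationships".

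**The concern.** The information script is itself randomised, so whoever delivers or omits it must already know that factor. If the envelope names one of the four combined groups, the same person learns the pill arm at the same moment. That person could then, without intending it, present the power of placebos with more conviction to a patient about to receive pills than to one who will receive none, or handle the diary instruction and the matched time differently.

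In this trial the encounter and the expectation it creates are part of what is being studied, and the primary outcome is a self-rated symptom composite. A difference in delivery by pill arm would be confounded with the placebo contrast. If it arose mainly through the script, it would also be confounded with the placebo-by-information term. These are the two hypotheses in section D, and the three-factor ANOVA in section F cannot separate such a difference from a true effect. Equal time with the practitioner does not equalise tone or conviction.

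**Working it through.** **Step 1: what must be known, and when.** This sets the parts of section E side by side.

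- Before the script: the information arm, because the script is either given or left out.
- During the script, the assessment and the diary instruction: nothing further. The script's last statement is conditional, so it can be read to any informed patient whatever the pill arm.
- At hand-out: the pill arm.

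The pill arm is therefore first needed at hand-out. An envelope naming the combined group makes it available before the script, and no sentence in the protocol withholds it from the practitioner.

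**Step 2: what the protocol leaves open.** It does not state the number of envelopes per patient, who opens them, when they are opened, or whether one person gives both the script and the pills. The finding is therefore that the protocol permits early knowledge of the pill arm. It does not say that this will happen.

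**Step 3: illustration of size.** The protocol has no figure to reproduce on this point.

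Inputs from the protocol: N = 60 in four groups (section E); two-sided alpha 0.05 (section F).

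Assumptions: equal cells of 15, since no ratio is stated; no true effect; a bias b in SD units of the change score. The values of b are assumed, because the protocol gives none.

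*Placebo contrast, 30 v 30.* SE = √(2/30) = 0.258 SD; df = 60 − 4 = 56; critical t = 2.003. The rejection rate is the two-sided tail of a noncentral t with noncentrality b/SE.

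A bias confined to the informed half (15 v 15) is halved in the 30 v 30 contrast: 0.2/2 = 0.10 and 0.3/2 = 0.15.

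| Where the bias acts | Shift in those patients | Shift in contrast | Noncentrality | Rejection rate |
|---|---|---|---|---|
| None | 0 | 0 | 0 | 5% |
| Informed half only | 0.2 SD | 0.10 | 0.10/0.258 = 0.39 | 6.7% |
| Informed half only | 0.3 SD | 0.15 | 0.15/0.258 = 0.58 | 8.8% |
| All patients | 0.2 SD | 0.20 | 0.20/0.258 = 0.77 | 11.9% |
| All patients | 0.3 SD | 0.30 | 0.30/0.258 = 1.16 | 20.8% |

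*Placebo-by-information term.* This is the pill difference in informed patients minus that in uninformed patients. SE = √(4/15) = 0.516 SD. A bias of 0.2 or 0.3 SD in the informed half only gives noncentrality 0.2/0.516 = 0.39 or 0.3/0.516 = 0.58, so the same 6.7% and 8.8%. A bias equal in both halves cancels from this term.

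*Direction.* A stronger script for informed pill patients would favour placebo in the main contrast. It would also tend to create an interaction, whereas section D predicts none.

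**The case against.** **A categorical reading goes beyond the text.** A reader might infer that there is one envelope per patient and that the practitioner does know the pill arm during the script. The protocol says neither. The script's conditional wording fits a procedure in which the pill arm is still undisclosed to everyone in the room. This stands, and it limits the finding to what the protocol allows. It does not remove the finding, because the natural reading of an envelope showing the group assignment is the combined group, and nothing rules that reading out.

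**The contact is not promised to be identical.** Section E promises equal time and section B speaks of comparable relationships. This also stands as to wording. Even so, the controls are to be handled like the placebo group apart from the pills, and that aim is weakened if handling can vary with knowledge of the pill arm.

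**The larger error rates overstate the main mechanism.** A reader might take 12% to 21% as the expected consequence. Those figures need the full assumed bias in uninformed patients too, who hear no script. For a bias through the script alone, 7% to 9% is the matching range.

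**The remedy is partial and the script is constrained.** From hand-out onward both patient and practitioner know the pill arm, through two weeks and the final self-rating. The four statements are also fixed to match earlier studies, which limits differences in content, though not in tone. Both points are right. They make the gain modest, but the part of the visit before hand-out can still be protected.

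**It is not free.** A second envelope and a slightly longer procedure are needed, so the cost is small but not nil.

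**Conclusion.** The point holds in a limited form. The allocation rule, read naturally, permits the person giving the script to know the pill arm before it is needed, and the protocol contains no safeguard against this. It is an avoidable source of differential delivery that can enter both hypotheses of a trial with a self-rated primary outcome.

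Its size is unknown. Under the stated assumptions (equal cells, no true effect, an assumed shift of 0.2 to 0.3 SD), the false-positive rate of the placebo contrast rises from 5% to about 7% to 9% if only the informed half is affected, and to about 12% to 21% if all patients are. The interaction term rises to about 7% to 9% in the first case and stays at 5% if the bias is equal in both halves.

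The protocol does not support saying that the practitioner certainly knows the pill arm, or that any such bias is present. This is a cheap improvement to the procedure, and it does not show that the design is invalid.

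**What to change.** Keep the same four-arm randomisation list and disclose it in two stages:

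- an outer sealed envelope showing only information or no information, opened before the script is due;
- an inner sealed envelope showing only placebo or no placebo, opened after the baseline assessment, the script (or its omission), the diary instruction and the matched contact are finished.

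Add to section E who opens each envelope and when, and that the practitioner does not know the pill arm until the inner one is opened. If the pill arm is already revealed that late in practice, that statement alone settles the point.

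The cost is one extra envelope per patient (60 in all), a short addition to section E and a slightly longer procedure. Sample size, visits and analysis do not change. The change protects only the part of the visit before hand-out.
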